### Qualitative Analysis Plan

Qualitative data from postintervention interviews will be analyzed using a reflexive thematic analysis approach to explore participants’ experiences with the SAFE-CaPS mHealth app. All interviews will be transcribed verbatim by a professional transcription service with established safeguards to protect Protected Health Information, and transcripts will be coded using ATLAS.ti v24 (Lumivero/ATLAS.ti Scientific Software Development GmbH). Two researchers (MO and GK) will independently review transcripts, develop initial codes, and iteratively refine a shared codebook through discussion and consensus. Codes will then be organized into broader categories and themes that capture perceptions of usability, acceptability, cultural relevance, and factors influencing engagement with the intervention, with attention to variation across ethnic subgroups. Emerging themes will be reviewed collaboratively with the research team to ensure analytic rigor. Qualitative findings will be integrated with quantitative outcomes using an explanatory sequential mixed-methods approach, allowing qualitative insights to contextualize, explain, and complement observed quantitative patterns to provide a comprehensive understanding of intervention usability and impact.

### Study Compensation

Participants (N=248) will receive US $50 each for completing both the baseline and postintervention assessments, totaling US $100 per participant. In addition, all participants will receive US $25 for completing each interim survey at 3, 6, and 9 months (a total of US $75). Participants in the SAFE-CaPS arm who complete the semistructured exit interview (n=30) will receive an additional US $50 payment. To enhance EMA compliance, SAFE-CaPS participants (n=124) will receive US $2 per day for completing daily assessments once a day over 15 weeks (up to US $210) and US $20 per completed weekly assessment (up to US $300). Thus, participants in this arm may earn up to US $685, or US $735 if they also complete the exit interview. Participants in the control arm may earn up to US $175 in total. Compensation will be provided weekly via a reloadable study credit card [74]. Participants will not be compensated for on-demand app usage or engagement with intervention components. Although the total potential payment varies by arm, the additional amounts in SAFE-CaPS accurately reflect the increased time and effort required for intensive EMA data collection. This structure was reviewed and approved by the University of Oklahoma Health Campus Institutional Review Board (IRB). To guard against bias, total compensation received will be captured and evaluated as a covariate in sensitivity analyses.

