**Methods:**

This 12-month stratified randomized clinical trial will enroll 248 Black survivors with CaP (including native born, African-born, and Caribbean-born men) into the SAFE-CaPS intervention arm and standard care (SC) control group (1:1 allocation). Eligible participants are self-identified Black men (including native born, African-born, and Caribbean-born) aged 40 to 80 years with a confirmed CaP diagnosis within the past 5 years who own or are willing to use a smartphone. SC will consist solely of routine oncology or primary care follow-up, including clinic visits, referrals, and supportive services as needed, with no digital components. The SAFE-CaPS intervention, developed using the Insight platform, includes daily and weekly ecological momentary assessments of pain, urinary and bowel symptoms, sleep, fatigue, sexual function, mood, physical activity, and diet; adaptive educational modules addressing treatment-related side effects and culturally grounded survivorship concerns; automated symptom alerts prompting nurse follow-up and provider notification; and engagement features such as reminders, goal-setting, and literacy-appropriate content. Intervention content incorporates culturally tailored messaging, patient narratives, and feedback from prior qualitative work with ethnically diverse Black CaP. Stratified randomization will ensure balanced representation of ethnic subgroups. Primary outcomes include overall QoL. Secondary outcomes include specific symptom domains, mental health (depression and anxiety), health care engagement, and app acceptability. Assessments will occur at baseline, 3, 6, 9, and 12 months, and linear mixed models with intent-to-treat principles will evaluate intervention effects over time.

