#### Secondary Outcomes

App engagement and usability will be evaluated based on frequency and duration of use, symptom-tracking interaction, and engagement with educational content. Technology acceptance and behavioral intent will also be assessed using the UTAUT framework, which evaluates performance expectancy, effort expectancy, social influence, and facilitating conditions. These outcome variables will be analyzed at multiple time points to determine the effectiveness of the SAFE-CaPS intervention in enhancing QoL, improving mental health, and supporting symptom self-management among Black survivors with CaP. Additionally, semistructured interviews and focus groups will be conducted to explore app usability, engagement, and perceived benefits.

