#### Analytic Plan

The statistical analyses for the SAFE-CaPS study will include descriptive, bivariate, and multivariate methods to assess the intervention's impact on QoL, mental health, symptom management, and app engagement. Each variable will be examined for distribution, range, mode, median, and mean (SD). Skewness and kurtosis will be determined for all ratio-level variables, while frequency distributions will be calculated for nominal- and ordinal-level variables. Descriptive statistics will be used to summarize all study variables, and bivariate statistics will be computed to assess relationships among theoretical constructs.

Differences in demographic and clinical characteristics between the 2 groups will be analyzed using a 2-tailed independent *t* test, Fisher exact test, and the chi-square test. Intervention usage will be analyzed using descriptive and inferential statistics for the number of EMAs completed, alerts triggered, and views of the educational section. An adjusted linear regression mixed-effect model will assess the impact of treatment group assignment on FACT-P scores at 12 months, adjusting for relevant covariates such as age, socioeconomic status, treatment type, ethnicity, and cancer stage. Preliminary analyses will include checks for multicollinearity and score distributions to ensure model validity. The goal is to determine the effect of the intervention on QoL as measured by FACT-P, independent of these baseline characteristics.

Chi-square analyses and *t* tests will examine baseline differences between ethnic groups. One-way ANOVA and correlations will be conducted to determine whether demographic and clinical variables are significantly associated with perceived acceptability, accessibility, and engagement. Due to the preliminary nature of these analyses, only covariates significant at *P*<.05 will be included in the final models. Cronbach α will assess the reliability of the multi-item instrument to determine the internal consistency of the model used to measure the constructs of the proposed framework, as shown in Figure 3. A Cronbach α value ≥0.70 will be considered acceptable for internal consistency [73]. Data will be analyzed using SPSS (version 29; IBM Corp).

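### The article says engagement with intervention components is unpaid, yet pays up to $510 per man for EMAs it describes as part of the intervention; EMA and alert counts therefore measure incentivised compliance

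*Protocol article*

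**What the plan says.** **Payment.** Under Study Compensation: "To enhance EMA compliance, SAFE-CaPS participants (n=124) will receive US $2 per day". Each weekly assessment earns a further $20. The section presents these sums as payment for the burden of EMA data collection and then adds: "Participants will not be compensated for on-demand app usage or engagement with intervention components". Total compensation is to be examined as a covariate in sensitivity analyses.

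**What the intervention is.** The Methods paragraph of the Abstract says that SAFE-CaPS "includes daily and weekly ecological momentary assessments of pain, urinary and bowel symptoms, sleep, fatigue, sexual function, mood, physical activity, and diet". The Intervention (SAFE-CaPS) section likewise treats daily symptom assessments as SAFE-CaPS content. There, reported symptoms trigger alerts, and alerts bring up adaptive educational material.

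**What is counted as engagement.** Secondary Outcomes: "App engagement and usability will be evaluated based on frequency and duration of use, symptom-tracking interaction, and engagement with educational content". The Analytic Plan will analyse intervention usage with descriptive and inferential statistics "for the number of EMAs completed, alerts triggered, and views of the educational section".

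**The concern.** The compensation sentence assures the reader that use of the intervention was not paid for. If EMAs are intervention content, the assurance fails for that content, and the first-named usage measure is one the trial pays for directly.

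This bears on what the trial may conclude. The Results section anticipates high engagement, including frequent symptom tracking. The Abstract's conclusion looks ahead to real-world implementation, where nothing in the article suggests that men would be paid to answer EMAs. A completion rate obtained under payment, if reported as engagement, says little about unpaid use. The Analytic Plan also relates demographic and clinical variables to engagement. If response to payment varies with socioeconomic position, those associations would partly describe response to money. The documents do not show whether or how much it varies.

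**Working it through.** **1. Reproduce the plan's payment figures** (all inputs from Study Compensation). The daily rate is stated as: "will receive US $2 per day for completing daily assessments once a day over 15 weeks".

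- Daily EMAs: $2 × 7 × 15 = $210, as stated.
- Weekly EMAs: $20 × 15 = $300, as stated.
- Surveys, both arms: 2 × $50 + 3 × $25 = $175, the stated control maximum.
- SAFE-CaPS maximum: $175 + $210 + $300 = $685, as stated; with the $50 exit interview, $735, as stated.

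**2. Size of the EMA-contingent part.**

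- $210 + $300 = $510 per man.
- $510 / $685 = 74% of the maximum without the interview.
- $685 − $175 = $510, so EMA pay is the whole difference between the arms' maxima.
- In a fully completed paid week: 7 × $2 + $20 = $34.

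**3. Each usage measure against the payment rule.**

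| Measure (Analytic Plan) | Paid? |
|---|---|
| EMAs completed | Yes, directly |
| Alerts triggered | Indirectly: triggered by symptom reports, largely made in paid EMAs |
| Education views | Not directly; some follow alerts, others can come from browsing the content library |

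On-demand use, which would fall under frequency and duration of use in Secondary Outcomes, is unpaid.

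**4. Can the total-compensation covariate separate paid from voluntary use?** For a man with *d* daily EMAs, *w* weekly EMAs and *k* interim surveys who completes both $50 assessments, pay = 100 + 25*k* + 2*d* + 20*w*. Within the SAFE-CaPS arm only *k* varies apart from EMA completion, so adjusting EMA counts for pay comes close to adjusting a variable for itself.

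An illustrative simulation shows the degree. Its assumptions are not from the documents: mean EMA completion of 50%, 70% or 90%, beta-distributed between men (parameters summing to 5), the same rate for daily and weekly EMAs, 85% completion of interim surveys, all $50 assessments completed, and 124 men per arm.

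| Mean EMA completion | Correlation of pay with EMA count (SAFE-CaPS arm) | Correlation of pay with arm | Variance inflation, 1/(1 − r²) |
|---|---|---|---|
| 50% | 0.95 | 0.85 | 3.6 |
| 70% | 0.95 | 0.93 | 7.0 |
| 90% | 0.94 | 0.98 | 22.8 |

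Within the arm the covariate nearly duplicates EMA completion; across arms it is largely a proxy for allocation.

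**5. Paid weeks against the assessment and access calendars.** The Daily EMAs section schedules 12 weeks plus one week after each of the 6-, 9- and 12-month assessments: 12 + 3 = 15 weeks, or 105 days, the same number that is paid. Study Recruitment and Procedure gives 12 months of app access; Daily EMAs gives 12 weeks. On the 12-month reading, paid days cover 105/365 = 29% of access. On the 12-week reading, every week of access is paid.

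**The case against.** The strongest reply is that nothing is hidden. The EMA payment and its purpose stand a few sentences before the disputed one, and the article also treats EMAs as measurement: in the EMA section, in Table 1 and in its reference to intensive data collection. On that reading the sentence separates paid assessment from unpaid use of the app. The dual role is real and the wording looks loose rather than misleading. It does not make the sentence true, because the article also places EMAs in the intervention and counts them as its usage.

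It can also be said that detailed engagement definitions belong in a fuller plan that is not shown. That holds for detail. Here, though, the article makes a positive statement that it contradicts, and it names the usage measures.

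A reader might go further and infer that no engagement or persistence result can be read as voluntary. The documents do not support this:

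- On-demand use and unprompted education views carry no payment.
- Symptom-tracking interaction is not defined and could include the separate facility to log and share symptoms.
- Persistence is not a named outcome.
- Acceptability is also assessed by the 12-month UTAUT survey and the exit interviews.

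A reader might equally take the 52 − 15 = 37 weeks without EMA pay as a clean view of voluntary use. That does not hold either. It presumes 12-month access. Daily EMAs are also scheduled for about the same weeks that are paid, so a fall in tracking after week 12 could come from the end of prompts as much as the end of pay.

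Payment was considered in the plan: as a sensitivity covariate, and under Strengths and Limitations as a possible cause of differential retention. Neither addresses payment as a driver of engagement.

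**Conclusion.** The point holds for two of the three usage measures named in the Analytic Plan. EMA counts are paid directly, at up to $510 per man, and alert counts follow largely from those entries; both should be read as incentivised compliance. Education views are mixed: those prompted by EMA-triggered alerts share the problem, and unprompted ones do not. The compensation covariate does not repair this. That follows from how pay is calculated; only the exact correlations depend on the simulation's assumptions.

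The documents do not allow an estimate of how far payment raises completion. Paying for EMAs is not itself a fault. The fault lies in the statement that engagement with intervention components is unpaid and in usage measures that do not distinguish paid from unpaid behaviour. The consequence is confined to secondary engagement findings and the scalability statements drawn from them.

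**What to change.** 1. In Study Compensation, correct the sentence to say that EMA completion, which is part of the intervention, is paid, and that on-demand use and viewing of educational content are not.
2. In Secondary Outcomes and the Analytic Plan, report EMA completion, and the alerts and education views it triggers, as incentivised assessment compliance.
3. Base statements on voluntary engagement and scalability on unpaid, unprompted use: on-demand opens, self-initiated symptom logs and education views not prompted by an alert, as far as the app logs distinguish them.
4. Reconcile the 12-month and 12-week access periods before any engagement window is set, and do not present paid against unpaid weeks as a clean comparison.
5. Do not rely on total compensation as a covariate to separate paid from voluntary use.

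Payments need not change. The cost is rewording three sections and a split of the app logs. The article does not say whether the logs can tell prompted from self-initiated use, so this must be checked first. The headline engagement figure will probably be lower. With 6 of 248 men reported as enrolled, the definitions can be settled before there are engagement results to report.

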### Ethical Considerations

The SAFE-CaPS study will adhere to strict ethical guidelines to protect participants’ rights, privacy, and safety. The study protocol has been approved by the University of Oklahoma Health Campus Institutional Review Board (OUHC IRB; protocol number 17116). This trial is registered at ClinicalTrials.gov (NCT06651359). All participants will provide written informed consent after being fully informed of the study purpose, procedures, risks, benefits, and voluntary nature of participation, including the right to withdraw at any time without penalty.

To protect privacy and confidentiality, all participant data will be deidentified, encrypted, and stored on secure, password-protected computers and servers. Audio-recorded interviews will be professionally transcribed, and all transcripts will be deidentified. Only authorized study personnel will have access to identifiable data. Additional protections, including user access controls, password authentication, auto-logout features, and audit trails, will be implemented to prevent unauthorized access to Protected Health Information. Participants who experience distress or report clinically concerning symptoms will be referred to appropriate health care providers, and the app’s automated alert system will notify the study team when severe symptoms are reported to facilitate timely follow-up. Ethical oversight will be maintained through ongoing IRB monitoring and adherence to all federal and institutional regulations governing human subjects’ research. Participants will receive monetary compensation for completing study assessments across the 12-month period, with payments distributed at each assessment point. Participants in the SAFE-CaPS arm may earn up to US $685, or up to US $735 if they complete the exit interview, whereas participants in the control arm may earn up to US $175 in total.

## Results

The SAFE-CaPS study received funding in January 2024, and IRB approval was received in May 2024. Study recruitment began on August 24, 2025. Overall, 6 participants have been enrolled, including 2 in the SAFE-CaPS intervention arm and 4 in the SC group. Recruitment is expected to conclude in July 2027. Data analysis is anticipated to occur toward the end of 2027, with article preparation and publication planned for mid-2028 and early 2029. The SAFE-CaPS study is expected to improve QoL, mental health, and symptom management among ethnically diverse Black men with CaP. It is anticipated that participants in the intervention group will demonstrate significant improvements in FACT-P scores, along with reductions in depression and anxiety symptoms over time. Real-time symptom monitoring is expected to enhance self-management and facilitate timely intervention, resulting in fewer severe symptom episodes and improved health outcomes. High app engagement is anticipated, with frequent use of symptom tracking, educational content, and provider alerts. Increased engagement may be associated with better health behaviors, including increased physical activity and improved dietary intake. Exploratory analyses may reveal differences in app adoption based on sociodemographic factors, enabling the identification of potential disparities in digital health use. Furthermore, qualitative findings are expected to provide insights into facilitators and barriers to app usability, informing future refinements of the intervention and guiding the scalability and adaptation of the SAFE-CaPS model for broader implementation.

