**Results:**

The study was funded in 2024, institutional review board approval was received in mid-2024, and the study began recruitment on August 24, 2025. Overall, 6 participants have been enrolled, with 2 in the SAFE-CaPS intervention and 4 in SC. Recruitment is expected to conclude in July 2027. Data analysis will occur in late 2027, with article preparation and publication planned for mid-2028 and early 2029. We hypothesize that SAFE CaPS participants will experience greater improvements in QoL, reduced symptom burden, and higher engagement in care compared to SC.

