### Sample Size and Power Analysis

The sample size required to detect a significant change in the primary outcome (FACT-P Total Score) was estimated using a 2-sample *t* test. Although FACT-P will be assessed at baseline and at 3, 6, 9, and 12 months, the sample size calculation was based on detecting a statistically significant difference between groups at the 12-month timepoint, which serves as the primary endpoint. The calculation assumed a significance level (α) of 0.05, 80% power, and a 1:1 randomization ratio. Based on prior research by Cella et al [72], which reported an effect size between 0.39 and 0.58, the sample size was conservatively determined using the smaller effect size (0.39). Under these assumptions, a minimum of 105 participants per group is required to detect a meaningful difference in FACT-P scores.

We anticipate that 15% of the full sample will be lost to attrition; therefore, the final target sample size was set at 124 participants per group (N=248 total). A participant sampling plan will be implemented to ensure adequate representation of ethnic groups and balanced allocation across intervention and control conditions, in alignment with the randomized controlled trial design.

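### Data analysis is dated late 2027, but recruitment to July 2027 with a 12-month primary endpoint puts the last primary outcome in July 2028

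*Protocol article*

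**What the plan says.** The timetable stands in two places. The Results section of the protocol article reports "Study recruitment began on August 24, 2025", then "Recruitment is expected to conclude in July 2027", then "Data analysis is anticipated to occur toward the end of 2027", "with article preparation and publication planned for mid-2028 and early 2029". The Results paragraph of the Abstract gives the same end of recruitment and says "Data analysis will occur in late 2027".

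The endpoint is fixed elsewhere. Sample Size and Power Analysis bases the calculation on a "difference between groups at the 12-month timepoint, which serves as the primary endpoint". The Analytic Plan says that its adjusted mixed model "will assess the impact of treatment group assignment on FACT-P scores at 12 months".

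On progress, Results states "Overall, 6 participants have been enrolled, including 2 in the SAFE-CaPS intervention arm and 4 in the SC group", without giving the date of that count. The article describes no interim analysis, no data cut-off before follow-up is complete, and no shortened follow-up for men who enrol late.

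**The concern.** A man enrolled in July 2027 has his month-12 FACT-P in July 2028. An analysis in late 2027 would come before that, and before the month-12 visit of everyone enrolled after about December 2026 at the latest. The end of recruitment, the 12-month endpoint and the analysis date are therefore incompatible.

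At stake is whether the trial delivers its own design figures. The target of 124 per arm covers 15% attrition and almost nothing else: 124 × 0.85 = 105.4, against 105 required. Men who are not yet due at month 12 come on top of attrition, and the sample size makes no allowance for them.

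**Working it through.** **Inputs.** From Results: recruitment starts on 24 August 2025 and ends in July 2027 (no day given, so 1 and 31 July are both used); analysis is in late 2027 (no day given, so 1 October to 31 December is used). From Sample Size and Power Analysis: endpoint at 12 months, α = 0.05 (sidedness not stated, two-sided assumed), 80% power, 1:1 allocation, standardised effect 0.39, 105 per group, 15% attrition, 124 per group. Uniform accrual is an assumption of this check; the article gives no accrual curve.

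**1. The plan's own figure.** Normal approximation: n = 2(1.960 + 0.842)² / 0.39² = 103.2, so 104 per group. The exact two-sample t test gives 104.18, rounded up to 105, and power at 105 is 80.3%. Attrition: 105 / 0.85 = 123.5, so 124. The stated sample size reproduces and is not in question.

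**2. Calendar, with no accrual assumption.** July 2027 + 12 months = July 2028. From a date between 1 October and 31 December 2027, the last month-12 visit (1 to 31 July 2028) is 6 to 10 months away. On 31 December 2027 a man enrolled in July 2027 has about 5 to 6 months of follow-up.

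**3. Share without a month-12 value, uniform accrual.** Let S be the start of recruitment, R its end and A the cut-off. Then

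f = (R − (A − 12 months)) / (R − S).

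Men per arm with the outcome after attrition = 124 × (1 − f) × 0.85. Power is that of a two-sided two-sample t test at 0.39 with that number per arm.

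| Recruitment ends | Cut-off | f | Men of 248 not yet due | Per arm after attrition | Power |
|---|---|---|---|---|---|
| 1 Jul 2027 | 31 Dec 2027 | 182/676 = 26.9% | 67 | 77.0 | 67.2% |
| 1 Jul 2027 | 1 Oct 2027 | 273/676 = 40.4% | 100 | 62.8 | 58.3% |
| 31 Jul 2027 | 31 Dec 2027 | 212/706 = 30.0% | 74 | 73.8 | 65.3% |
| 31 Jul 2027 | 1 Dec 2027 | 242/706 = 34.3% | 85 | 69.3 | 62.5% |
| 31 Jul 2027 | 1 Oct 2027 | 303/706 = 42.9% | 106 | 60.2 | 56.4% |

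Worked example, third row: 124 × (1 − 0.300) = 86.8 per arm have reached month 12, and 86.8 × 0.85 = 73.8.

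**4. Sensitivity to accrual.** Suppose the 6 men reported were enrolled by a date between 1 October 2025 and 1 March 2026 (assumed) and the other 242 uniformly afterwards. The share without a month-12 value is then about 28% to 40% at 31 December 2027 and 42% to 57% at 1 October 2027. Front-loaded accrual would shrink the gap. To close it at a 31 December 2027 cut-off, all 248 men would have to be enrolled by 31 December 2026: 494 days, or about 16.2 months, so 15.3 men per month. Uniform accrual to 31 July 2027 (706 days, 23.2 months) needs 10.7. The faster rate would also contradict the July 2027 date.

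**The case against.** The strongest reply is that these are forecasts in status text, hedged as expected or anticipated, while the Methods call throughout for quarterly assessments to month 12 and a model for FACT-P at month 12. Nothing in the design asks for truncated follow-up, so a misstated date is at least as likely as an intention to leave out late enrolees. That stands, and it makes this an inconsistency of dates rather than a flaw in the design. It does not remove the conflict, which appears in both the Abstract and Results. July 2027 might have been meant as the end of follow-up, but both places say recruitment.

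The article speaks of data analysis, not of a final analysis or database lock. That is correct; but no other analysis is named, and article preparation follows it, so the main analysis is the natural reading.

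The power figures come from complete cases, whereas the planned analysis is a covariate-adjusted mixed model. Late enrolees could contribute earlier visits, and their missing values would be administrative. This also stands: the loss under the planned model has not been calculated, and the figures illustrate the scale only. The men concerned would still lack the primary outcome itself.

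The existing registries might allow fast early accrual. That is possible, but the 6 men enrolled so far give no sign of it.

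A reader might also infer an unblinded early look, repeated later on full data with no control of type I error. The article does not support that: it describes no interim analysis or repeat analysis, and Study Randomization keeps the data analyst blinded to allocation.

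**Conclusion.** The point holds as an internal inconsistency. The only analysis date given falls 6 to 10 months before the last month-12 assessment that the stated recruitment period implies. This rests on the article's own dates and endpoint alone.

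The size depends on assumptions. With uniform accrual, cut-offs from 1 October to 31 December 2027 and recruitment ending on any day in July 2027, 27% to 43% of men lack the primary outcome, 60 to 77 per arm remain against 105, and complete-case t-test power is 56% to 67% against the stated 80%. A slower start makes this worse and a faster one makes it better.

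The documents do not show that the investigators intend to analyse an incomplete cohort, nor that an early comparison between arms is planned. They show only that the timetable, followed as written, would miss the trial's own sample size requirement.

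**What to change.** Correct the dates in the Results paragraph of the Abstract and in the Results section, in one of two ways:

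- Schedule the 12-month FACT-P analysis after the last randomised participant's month-12 assessment, about August 2028 if recruitment ends in July 2027, and move the mid-2028 start of article preparation to follow it.
- Keep the late-2027 analysis and bring the end of recruitment forward to about 12 months before it, that is, to late 2026.

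If the late-2027 work was meant only as data preparation, say so and give the date of the 12-month analysis separately.

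The first option costs a later analysis and leaves a shorter route to publication in early 2029. The second keeps the analysis date but demands accrual of about 15 rather than 11 men per month. Neither changes the design, the endpoint or the sample size.
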